***Inoculation***

• Inoculation - using a P200 micropipette, 0.1ml saline containing the desired dose (see
Figure 2) of pneumococcus will be instilled into the nose. The participant will be seated in a semi-recumbent position. After inoculation, the participant will remain in this position for up to 15 mins. They will be given a post-inoculation advice sheet (including emergency contact details), thermometer, a course of amoxicillin (500mg TDS for 3 days) and a daily symptom log to complete.

• Dose escalation and sham inoculation - We have adopted a step-wise approach to escalating the inoculation dose. The protocol is designed to: a) minimise the possibility that we try repeatedly to attain carriage at a dose in which it is unlikely to occur; b) maximise safety by inoculating small groups (in case adverse events occur) before continuing on to larger groups in which we will be able to give reasonable precision to estimate carriage rates. Groups 1, 2 and 3 will receive increasing doses of pneumococcal inoculation as explained in
Figure 2. Briefly, 20,000 cfu/naris (Group 1) is not expected to achieve carriage. If 80,000 cfu/naris achieves more than 4 from 9 participants with carriage, then the study will end at that point. Sham inoculation with 0.9% normal saline has been incorporated into the study design to assess whether any potential observed effects in participants are pneumococcal challenge-related or simply reflect the study conditions. Participants will receive only one inoculation dose. If carriage is not achieved after inoculation, participation will be concluded upon completion of visit eight.

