**Figure 2. f2:**
[figure not shown]
Dose escalation study design, adapted from Waddington
*et al*.
^12^. The doses for Groups 1, 2 and 3 will be 20000, 80000 and 160000 pneumococcal colony forming units (CFU) per naris respectively. All participants will be monitored for adverse effects and for pneumococcal carriage. The first cohort will be inoculated with 20,000 CFU/naris (
**Inoculation A**).
**†**: Eight participants will be randomised 3:1 to pneumococcal inoculation (n=6) or sham inoculation with 0.9% saline (n=2). If ≥2/6 participants from the initial cohort of eight develop experimental pneumococcal carriage, a further 4 participants will be recruited to this dose cohort.
*****: Four participants will be randomised 3:1 to pneumococcal inoculation (n=3) or sham inoculation with 0.9% saline (n=1). If the combined carriage rate of the completed cohorts is ≥4/9 (6+3 nasally challenged with pneumococcus), then the nasal challenge dose will be established, and we will conclude the study. If at either of these decision points, the carriage rate is insufficient, the algorithm will be restarted with a higher challenge dose of 80,000 CFU/naris (
**Inoculation B**) and the recruitment schedule repeated. If at 80,000 CFU, the carriage rate is insufficient, then an additional cohort of participants will be recruited to the 160,000CFU/naris dose escalation group (
**Inoculation C**).
**‡**: 12 participants will be randomised 3:1 to pneumococcal inoculation (n=9) or sham inoculation with 0.9% saline (n=3). We have previously demonstrated 50-60% carriage rates with the 80,000 CFU 6B dose in the Liverpool pneumococcal controlled human infection model
^6,
13^.

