Figure 2 since an alternative participant will be recruited in the case of withdrawal of a participant. Participants missing study visits so that no day 2, 7 or 14 data is available will be withdrawn from the study and their data excluded from data analysis. A new participant will be recruited in such a case and this new participant will be allocated to the same pneumococcus / sham inoculation as the participant ID for the withdrawn participant was randomised to. The primary feasibility endpoint will be assessed, at each of the five analysis time points using colonisation results data from all participants that are required for that stage’s analysis and that have completed visit 7 (d14). Other analyses are primarily descriptive or make use of censored data techniques, so that no advanced missing data methods will be used in these analyses. Data collection forms are provided in extended data
^21^. 

***Statistical significance and multiple testing.*** Success (feasibility) of the study will be decided according to the decision rules stated on
Figure 2.

Success (safety) of the study will decided by decision of the DSMB & TC upon revision of each SAE and SUSAR. For this reason, no formal null hypothesis significance testing will be performed for the main analysis and no multiple testing adjustment will need to be made.

For secondary analyses, statistical significance is defined as p<0.05, but effect sizes / parameter estimates, exact p-values and confidence intervals will be stated. While we will report on statistical significance, results will be presented and discussed in accordance with recent guidance
^22^.

***Technical details.*** All analyses and figures will be performed using the R environment (v.3.5.3 or later) for statistical computing and graphics and associated packages
^23^.

***Feasibility.*** The primary analysis aims to establish feasibility of the Malawi CHIM: does one of the three doses (20,00, 80,000, 160,000 CFU) lead to ≥50% nasal colonisation?

To assess this, the decision algorithm specified in the study design (

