### Study status

At time of manuscript submission (23
^rd^ January 2020), the study has commenced recruitment and has currently inoculated eight participants at the 20,000 CFU dose

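### The Inoculation section ends the study at 80,000 CFU on more than 4 of 9 carriers, but the governing Figure 2 rule is at least 4 of 9

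*Protocol article*

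**What the plan says.** The Inoculation section, in its paragraph on dose escalation and sham inoculation, refers the reader to Figure 2 and then summarises the rule: if the 80,000 CFU dose "achieves more than 4 from 9 participants with carriage, then the study will end at that point".

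The Figure 2 legend sets out the algorithm in full.
- First stage: "If ≥2/6 participants from the initial cohort of eight develop experimental pneumococcal carriage, a further 4 participants will be recruited to this dose cohort".
- Second stage: "If the combined carriage rate of the completed cohorts is ≥4/9 (6+3 nasally challenged with pneumococcus), then the nasal challenge dose will be established", and the study then concludes.
- If the count is too low at either point, "the algorithm will be restarted with a higher challenge dose of 80,000 CFU/naris", with the same recruitment schedule. If 80,000 CFU also falls short, a further cohort goes to 160,000 CFU.

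On precedence, the Statistical analysis section (Statistical significance and multiple testing) states: "Success (feasibility) of the study will be decided according to the decision rules stated on" Figure 2. The Feasibility paragraph repeats that the Figure 2 algorithm is followed, and the Stopping criteria section ties completion of the protocol to the same figure.

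The Feasibility paragraph also words the primary question as: "does one of the three doses (20,00, 80,000, 160,000 CFU) lead to ≥50% nasal colonisation". The Study aims and the Study hypothesis put the target more loosely, at about 50%.

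**The concern.** The two rules concern the same dose, the same nine challenged participants and the same decision, but they set different cut-offs: 5 of 9 in the running text and 4 of 9 in the legend. This count is the whole primary analysis. The article states that no power was calculated and that the main analysis involves no formal test, so nothing else settles the decision if the count falls between the two rules.

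At exactly 4 of 9, Figure 2 calls the dose established and ends the study. A team working from the Inoculation sentence would not stop. The only onward path in Figure 2 is the 160,000 CFU group: 12 more volunteers, 9 of whom receive live pneumococcus at twice the dose. The Abstract says the design is meant to avoid unnecessary exposure, and this would be exposure that the governing rule does not call for.

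The wording of the feasibility question makes the slip harder to dismiss. A requirement of at least 50% agrees with 5 of 9 and not with 4 of 9. A reader trying to reconcile the texts would find two statements on one side and the governing rule on the other.

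**Working it through.** **Inputs**
- First stage at a dose: 6 challenged and 2 sham; continue if at least 2 of 6 carry (Figure 2 legend).
- Second stage: 3 more challenged and 1 sham; decide on the combined 9 (Figure 2 legend).
- Threshold: at least 4 of 9 (Figure 2 legend) or more than 4 of 9, i.e. at least 5 (Inoculation).
- Carriage at 80,000 CFU: 50% (Study hypothesis; Sample size justification), with a Liverpool range of 50–60% (Figure 2 legend). A rate of 40% is added here as an assumption, to show a lower case.

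**The plan's own figures reproduce.** Three doses × (8 + 4) = 36 participants, the stated maximum. The number of looks runs from 2 (both stages at the first dose, then stop) to 2 + 2 + 1 = 5, as stated in Timing of analyses. The algorithm has therefore been read as intended.

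**Observed rates at the two cut-offs**
- 4/9 = 44.4%, exact 95% interval 13.7% to 78.8%.
- 5/9 = 55.6%, exact 95% interval 21.2% to 86.3%.

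**How often the two wordings disagree.** Let X1 ~ Bin(6, p) and X2 ~ Bin(3, p), independent. The wordings part only if X1 ≥ 2 and X1 + X2 = 4. There are C(9,4) = 126 ways to place 4 carriers among 9. Those that fail the first stage have X1 = 1 and X2 = 3, which is 6 × 1 = 6 ways. That leaves 120, so

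P(reach stage two and end at exactly 4/9) = 120 · p⁴ · (1 − p)⁵.

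At p = 0.50 this is 120/512 = 0.234.

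**Chance that the dose is declared established.** At p = 0.50, at least 5 of 9 has probability 256/512 = 0.500. All such outcomes pass the first stage, because the second stage adds at most 3. Adding the 120 outcomes at exactly 4 gives 376/512 = 0.734.

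| True carriage p | P(stop), ≥4/9 | P(stop), ≥5/9 | Difference = P(exactly 4/9) |
|---|---|---|---|
| 0.40 | 0.505 | 0.267 | 0.239 |
| 0.50 | 0.734 | 0.500 | 0.234 |
| 0.55 | 0.824 | 0.621 | 0.203 |
| 0.60 | 0.893 | 0.733 | 0.159 |

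These are joint probabilities of passing the first stage and ending at 4, given that the study reaches 80,000 CFU. Conditional on passing the first stage, the p = 0.50 value is 0.234/0.891 = 0.263, where 0.891 is P(X1 ≥ 2).

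**The case against.** The strongest reply is that the document already resolves the conflict. The Inoculation sentence is a brief summary that sends the reader to Figure 2, and the Study design, Statistical analysis and Stopping criteria sections all defer to that figure. A wrong decision needs a team to act on one summary sentence against all of these. This stands. It shows which text to correct, and it is why the percentages above must not be read as an error rate.

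The Inoculation sentence is also not a strict logical contradiction. It says what happens above 4 and is silent on exactly 4, so it does not itself order escalation there. That is true, but most readers would take a stated stopping threshold as the threshold.

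The feasibility wording can be defended too. A cut-off on nine people need not equal the target rate. Exactly 50% cannot be observed with nine, 4/9 and 5/9 lie equally far from it, and both exact intervals contain it. A target of about 50% is compatible with at least 4 of 9. This weakens the feasibility wording as evidence that 5 of 9 was meant. It does not remove the mismatch, because the paragraph asks for at least 50% and then assesses this by a rule that passes 44.4%.

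Finally, the article does not prove what was intended. That Figure 2 governs is clear. That 4 of 9 was the number meant is a reading of that precedence, and the fix allows for the other answer.

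**Conclusion.** The concern holds. The stopping threshold at 80,000 CFU in the Inoculation section does not match the Figure 2 rule that the protocol makes decisive. As the document stands, at least 4 of 9 governs and the Inoculation sentence is wrong. The feasibility question, with its floor of 50%, should be aligned as well.

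The discrepancy bites at one outcome only, but a likely one: between 15.9% and 23.4% across the 50–60% range that the protocol cites, and 23.9% at 40%. These figures assume that the study reaches 80,000 CFU, that participants respond independently at a common rate, and that both stages are run as the legend describes. An actual wrong decision also requires the summary sentence to be applied in place of Figure 2, and the documents give no basis for putting a probability on that. The point should be fixed because it sets an escalation boundary in a live challenge study and is easily corrected. It does not undermine the design.

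**What to change.** 1. In the Inoculation section, change the 80,000 cfu/naris criterion to 4 or more of 9 participants with carriage.
2. In the Feasibility paragraph, replace the floor of 50% with approximately 50%, defined operationally as at least 4 of 9 under Figure 2.

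If the investigators in fact intended 5 of 9, amend the Figure 2 legend to at least 5 of 9 instead and leave the other two statements alone. In that case the chance of declaring a dose with true 50% carriage established falls from 0.734 to 0.500, so the choice should be made knowingly.

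Either way, settle it before any 80,000 CFU carriage result is read, so that the threshold cannot appear to have been chosen after the data. The Study status section reports that at submission the study "has currently inoculated eight participants at the 20,000 CFU dose", so at that point there was still time. The cost is a short protocol amendment, with no added participants or procedures.

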**Figure 2. f2:**
[figure not shown]
Dose escalation study design, adapted from Waddington
*et al*.
^12^. The doses for Groups 1, 2 and 3 will be 20000, 80000 and 160000 pneumococcal colony forming units (CFU) per naris respectively. All participants will be monitored for adverse effects and for pneumococcal carriage. The first cohort will be inoculated with 20,000 CFU/naris (
**Inoculation A**).
**†**: Eight participants will be randomised 3:1 to pneumococcal inoculation (n=6) or sham inoculation with 0.9% saline (n=2). If ≥2/6 participants from the initial cohort of eight develop experimental pneumococcal carriage, a further 4 participants will be recruited to this dose cohort.
*****: Four participants will be randomised 3:1 to pneumococcal inoculation (n=3) or sham inoculation with 0.9% saline (n=1). If the combined carriage rate of the completed cohorts is ≥4/9 (6+3 nasally challenged with pneumococcus), then the nasal challenge dose will be established, and we will conclude the study. If at either of these decision points, the carriage rate is insufficient, the algorithm will be restarted with a higher challenge dose of 80,000 CFU/naris (
**Inoculation B**) and the recruitment schedule repeated. If at 80,000 CFU, the carriage rate is insufficient, then an additional cohort of participants will be recruited to the 160,000CFU/naris dose escalation group (
**Inoculation C**).
**‡**: 12 participants will be randomised 3:1 to pneumococcal inoculation (n=9) or sham inoculation with 0.9% saline (n=3). We have previously demonstrated 50-60% carriage rates with the 80,000 CFU 6B dose in the Liverpool pneumococcal controlled human infection model
^6,
13^.

### Randomisation

Randomization has been included to prepare (test feasibility) for future vaccine studies. The clinical team and participants will be blinded to the allocation to avoid bias in the collection and evaluation of data during the study. The randomisation code will be produced by the MLW Statistical Support Unit (co-investigator [name]) using a computer-generated pseudo-random permutation procedure. Prior to the start of the study, a copy of the randomisation code will be supplied to the MLW laboratory team using sealed envelopes to enable the production of
*Streptococcus pneumoniae* inoculations and sham inoculations as required by the randomisation schedule. The laboratory team will not be blinded to the challenge allocation, this measure is to ensure participant safety and monitoring during follow up. Research team members will be assigned solely to one of two separate delegation logs for blinded and unblinded activities (clinical and laboratory).

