### Study endpoints

Primary endpoint: detection of the inoculated pneumococci by classical culture methods, at any time point, from nasal wash recovered from the participants at days 2, 7 and 14 following pneumococcal challenge.

Secondary endpoints: confirmation of robust clinical and laboratory methods for sample capture and processing. Acceptability of study and methods.

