### Study setting

Clinical procedures will be conducted at the Queen Elizabeth Central Hospital Research Ward, Blantyre, Malawi. Laboratory procedures will be conducted at the adjacent Malawi-Liverpool Wellcome Trust Clinical Research Programme Laboratories (MLW).

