### Determination of colonisation

Colonisation will be defined by the microbiology result of nasal washes taken at 2-, 7- and 14-days post inoculation. Nasal washes will be plated on to culture media and incubated overnight at 37°C in 5% carbon dioxide (CO
_2_). Colonies will be confirmed as
*S. pneumoniae* using classical microbiological techniques including (i) typical draughtsman-like colony morphology, (ii) the presence of α-haemolysis, (iii) optochin sensitivity and (iv) Gram-positive diplococci. Typing by latex agglutination will be done using a commercial kit to confirm pneumococcal serogroup. Isolates will be frozen at -80
^o^C for storage. Results from the cultured nasal wash will also be confirmed using polymerase chain reaction (PCR) based methods of bacterial detection.

Monitoring of colonisation – monitoring of colonisation will be performed by microbiology analysis of nasal washes.

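### The laboratory team that reads the culture-based primary endpoint is openly unblinded to challenge or sham, and no blinded reader is described

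*Protocol article*

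**What the plan says.** All of this is in the protocol article.

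- **Who is blinded, and why (Randomisation):** "The clinical team and participants will be blinded to the allocation to avoid bias in the collection and evaluation of data during the study".
- **Who is not (same section):** "The laboratory team will not be blinded to the challenge allocation, this measure is to ensure participant safety and monitoring during follow up". Before the study starts, "a copy of the randomisation code will be supplied to the MLW laboratory team using sealed envelopes to enable the production of" challenge and sham inocula.
- **How staff are separated (same section):** "Research team members will be assigned solely to one of two separate delegation logs for blinded and unblinded activities (clinical and laboratory".
- **What the primary endpoint is (Study endpoints):** "detection of the inoculated pneumococci by classical culture methods, at any time point, from nasal wash recovered from the participants" on days 2, 7 and 14. Determination of colonisation adds: "Colonisation will be defined by the microbiology result of nasal washes taken at 2-, 7- and 14-days post inoculation".
- **How a colony is identified (Determination of colonisation):** "i) typical draughtsman-like colony morphology, (ii) the presence of α-haemolysis, (iii) optochin sensitivity and (iv) Gram-positive diplococci", followed by latex agglutination for serogroup. Isolates are frozen and culture results are checked by PCR.
- **Where it is read (Study setting):** in the MLW laboratories. The MLW laboratory team is the one that receives the code.
- **What depends on it:** the Figure 2 legend and the Statistical analysis section leave the feasibility decision at each dose to the count of colonised challenged participants, with no further test.

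**The concern.** The purpose stated for blinding covers evaluation of data, but the most important evaluation in the study is the decision that a wash does or does not contain the inoculated pneumococcus. That decision is made in the laboratory, and the delegation logs place laboratory work on the unblinded side. As written, the reader may know which participants were challenged and which received saline.

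Culture reading involves judgement. The Safety considerations section puts natural colonisation at 40% of Malawian adults at any time, and the Screening section keeps natural carriers of other serotypes in the study. Some plates will therefore hold pneumococci that are not the challenge strain. A reader who knows the allocation could search harder, or pick more colonies for typing, in challenged washes. The endpoint is positive if any of three washes is positive, so reading errors can accumulate.

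At stake is the count that sets the dose. With six and then nine challenged participants per dose, one changed reading can reverse a decision.

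The safety reason given for unblinding is met if someone holds the code. It does not need that person to read the plates. Daily contact and emergency antibiotics are arranged for every participant, and the end-of-study antibiotic course depends on colonisation, not on allocation.

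**Working it through.** **Step 1. Side-by-side reading.** The purpose of blinding covers collection and evaluation of data. The people blinded are participants and clinical staff. The person evaluating the primary endpoint is a member of the laboratory team, which is unblinded as a whole. The article describes no blinded subgroup in the laboratory, no coded reading of washes and no separation of inoculum preparation from plate reading.

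**Step 2. Design figures.** Each dose uses 8 + 4 participants, of whom 6 + 3 are challenged. Three doses give 3 × 12 = 36 participants, 3 × 9 = 27 challenged and 9 sham. This reproduces the stated maximum of 36.

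**Step 3. Probability that a dose passes.** Let p be the true carriage rate and X the number of carriers among the first 6. The Figure 2 legend requires X ≥ 2, then at least 4 of 9 in total:

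P(pass) = Σ (x = 2 to 6) C(6,x) pˣ (1−p)⁶⁻ˣ × P(Bin(3,p) ≥ 4−x)

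At p = 0.30:
- x = 2: 0.3241 × 0.216 = 0.0700
- x = 3: 0.1852 × 0.657 = 0.1217
- x = 4, 5, 6: 0.0595 + 0.0102 + 0.0007 = 0.0705 (these already have 4)
- Sum: 0.262

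**Step 4. Add a misreading rate.** The documents give none. Assume a fraction f of truly negative challenged participants is read as positive, so that the rate seen is p′ = p + (1−p)f. For p = 0.30 and f = 0.05, p′ = 0.30 + 0.70 × 0.05 = 0.335, and the formula gives 0.344.

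| True carriage | p′ at f = 5% / 10% | P(pass), f = 0 | f = 5% | f = 10% |
|---|---|---|---|---|
| 20% | 0.240 / 0.280 | 0.082 | 0.142 | 0.219 |
| 30% | 0.335 / 0.370 | 0.262 | 0.344 | 0.430 |
| 40% | 0.430 / 0.460 | 0.505 | 0.579 | 0.649 |
| 50% | 0.525 / 0.550 | 0.734 | 0.782 | 0.824 |

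If errors are independent over the three washes, f = 5% per participant corresponds to 1 − 0.95^(1/3) = 1.7% per wash.

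**Limits of the calculation.**
- It shows false positives only. Expectation could also work the other way, for instance at the 20,000 dose, where the Inoculation section expects no carriage.
- It applies where recruitment is in two stages. The Figure 2 legend also describes a single block of 12 with 9 challenged, to which the two-stage formula does not apply.
- It uses the legend's threshold of at least 4 of 9, because the Statistical analysis section refers decisions to Figure 2. The Inoculation section words the 80,000 threshold as more than 4 of 9.

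**The case against.** **The choice is disclosed.** The article says openly that the laboratory is unblinded and gives a reason. A reader might infer that blinding was promised for every evaluation and then broken. The text does not support that, because its blinding sentence names only the clinical team and participants. This objection stands.

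**The endpoint is fairly objective.** A false positive must pass morphology, haemolysis, optochin and Gram stain, then serogroup typing and a PCR check. Isolates are frozen, so a positive call can be re-tested. Participants with natural 6B at baseline leave the study, so a natural carrier of another type would also have to be mistyped. This limits the bias but does not remove it: none of these steps is said to be read blind, the Statistical analysis section describes lytA qPCR as detecting the species, and a frozen isolate cannot correct a colony that was never picked.

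**The sham arm keeps its stated purpose.** The Inoculation section includes sham to show whether effects in participants come from the challenge or from study conditions. Symptoms are collected by blinded clinical staff, and the Figure 2 rule makes no comparison between arms. A reader might infer that unblinded reading destroys the value of the sham washes. It does not. It weakens them as a negative control for culture, for which the Statistical analysis section plans an estimate.

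**Blinding the reader would not remove all expectation.** Cohorts run in sequence and allocation is 3:1, so a blinded reader would still know the dose level and that three in four washes come from challenged participants. This stands. The gain is confined to concealing challenge versus sham for each wash.

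**The article is condensed.** Bench procedures may sit in SOPs that are not shown. That would answer a missing detail, but here the article itself states that the laboratory team is unblinded and divides the logs accordingly.

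**Conclusion.** The point holds as a design weakness measured against the protocol's own aim. Blinding does not reach the team that reads the primary endpoint, and that endpoint alone decides escalation and stopping apart from safety pauses.

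The size of any bias is unknown. Under the assumed 5% misreading rate, the probability of passing rises by 0.060 at 20% true carriage, 0.082 at 30%, 0.074 at 40% and 0.048 at the hypothesised 50%. These figures show sensitivity; they are not evidence that readings will be wrong.

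Two further inferences go beyond the text. The article does not say that the same individuals prepare inocula and read plates. It names one unblinded laboratory team and no other reader. Nor does it say that the DSMB holds the code.

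The change is worth making because it is cheap, and because randomisation was included to rehearse procedures for later vaccine studies, where blinded endpoint reading will matter more.

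**What to change.** For the cohorts still to be inoculated (the Study status section reports eight participants already inoculated at 20,000 CFU):

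1. Restrict the sealed code to the existing laboratory staff who prepare the inocula, and keep safety unblinding with them.
2. Put other existing laboratory staff, who process and read the day 2, 7 and 14 washes and the PCR, on the blinded delegation log.
3. Label washes with accession numbers that do not map to the randomisation list.

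The cost is a revised delegation log and a labelling step. Doses, visits and sample size do not change. The downside is a staffing constraint: whoever prepares an inoculum cannot read that participant's plates.

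If the laboratory cannot be split, the protocol should state that the primary endpoint is read unblinded and confine its claim about avoiding bias to the clinical data.
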